### Comorbidity-adapted exercise intervention

There will be three phases for the comorbidity-adapted exercise program: diagnostic, development, and intervention phases.

#### Diagnostic phase

After written informed consent, the research assistant will collect patient demographics (age, gender, marital status, weight, height, living arrangements, work history, education, highest degree, income, retirement status), medical history, and the participant’s pain history such as duration, trajectory, and symptomatology. A PHCP will then perform a physical and functional examination to determine contraindications and restrictions to an exercise program.

#### Development phase

The first exercise program session, provided by the trained PHCP, will involve a tailored session to adapt the exercise program to the older individual and provide patient education. The exercise program will consist of lower extremity and back extensor muscle-strength training, aerobic training, core stability exercises, balance training, and lower limb and back stretching based on an inventory. The details of the comorbidity-adapted exercise program are presented in Table 3. Adapting the exercise program for individual patients will include tailoring the exercise frequency, intensity, timing, and exercise type based on the presenting comorbid condition(s). Exercise adaptations will be based upon criteria developed from a previously conducted literature search by de Rooji et al. [23] that investigated restrictions, contraindications, and recommended adaptations of the target comorbidities. At this session, the PHCPs will provide patient education, explore the participant’s goals, motivations, and barriers to an exercise program, and provide the participant with paper-based GLA:D Back pain education material [33].

**Table 3 Tab3:** Description of the comorbidity-adapted exercise program for this feasibility study

Exercise description^a^	Time/dose/repetitions
**Global muscle stretching (whole body)**	**10 min**
**Comorbidity-adapted exercises**	**35 min**
*Muscle strengthening*	
Gluteals	
• Sit to stand	15 repetitions
• Chair squats	10 repetitions
• Standing leg extensions/pulses	10 repetitions/side
• Bridge	10 repetitions/3-s hold
Lumbar erectors	
• Isometric seated back extensions	10 repetitions/3-s hold
• Prone superman (bilateral and alternating unilateral)	5 repetitions/side
Lower extremity	
• Alternating lunges	5 repetitions/side
• Crab walk with resistance tubing	15 repetitions/side
• Standing straight leg abductions (with resistance tubing or isometric)	10 repetitions/side
*Muscle stretching/mobilisation*	
Lower extremity	
• Hamstrings, quadriceps, iliopsoas, gluteals	45 s/side
Lumbar erectors	
• Cat/cow	10 repetitions/2-s hold
• Cobra	45 s
*Core stabilisation*	
• Dead bug	Dependent on patient ability
• Quadruped	Dependent on patient ability
• Seated knee raises with core activation	15 repetitions/side
• Standing/sitting side crunches (weighted)	15 repetitions/side
*Balance training*	
• Standing on towel (progression with eyes closed)	Hold for 15 s each leg (5 repetitions/side)
**Aerobic training**	**15 min**
• Walking on treadmill or cycling	Dependent on patient ability/10 min
• Step ups	5 min

^a^Adapting the exercise program will include tailoring the exercise frequency, intensity, timing, and exercise type based on the presenting comorbid condition(s)

#### Intervention phase

The exercise program will consist of 16 exercise sessions over an 8-week program. There will be two supervised sessions per week with each session being approximately 60 min in duration. Sessions will be offered onsite at the Macquarie University, in a designated group exercise space. PHCPs will deliver multiple exercise sessions to participants within the program. The Borg Rate of Perceived Exertion scale will be used to monitor training intensity during each supervised exercise program session. Educational and coaching strategies will supplement the comorbidity-adapted exercise program throughout each supervised session [34], with adaptation to the exercise program patient directed.

### Data collection

Data will be collected in person by the research assistant at baseline, 4 weeks, and at 8 weeks after the first exercise program session. Patient demographics and outcome measurement data will be collected in the REDCap — Research Electronic Data Capture system and exported to an Excel spreadsheet. De-identified data will then be imported to STATA/IC® (StataCorp, Texas) for analysis. Qualitative interviews will be performed at 8 weeks, and interview data will be stored securely and transcribed verbatim.

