### Participants

In determining the sample size for progression criteria for a pragmatic pilot randomised controlled trial, CTs using a red/amber/green approach, we used the estimation from Lewis et al. [32] with an upper limit red zone (unacceptable) of 45% and a lower limit green zone (acceptable) of 75% for the feasibility outcome protocol adherence (Table 2). The test is a 1-tailed test with suggested alpha (*α*) of 0.05 and beta (β) of 0.1 [32]. Therefore, our target sample size is 24 participants. Participants must have at least one of the following target comorbidities: coronary heart disease, hypertension, type 2 diabetes, obesity, chronic obstructive pulmonary disorder, and depression (diagnosed by a medical specialist). There will be no cost to participants to undertake the exercise program as part of the study.

**Table 2 Tab2:** The traffic light system for progression criteria of this feasibility study to randomised controlled trial

	Green	Amber	Red
**Trial recruitment**	Recruitment of 24 participants with low back pain and comorbidity within 3 months	Recruitment of 24 participants with low back pain and comorbidity within 3–6 months	Twelve participants with low back pain and comorbidity are *not* recruited within 6 months
	At least 75% retention of participants through follow-up	At least 50% retention of participants through follow-up	Less than 45% retention of participants through follow-up
**Protocol adherence**	At least 75% of participants complete more than half of the exercise program sessions	At least 50% complete more than half of the exercise program sessions	Less than 45% complete more than half of the exercise program sessions
**Outcome data**	At least 80% of participants do not find the outcomes so burdensome that they would not participate in the study again	At least 70% of participants do not find the outcomes so burdensome that they would not participate in the study again	Less than 70% of participants do not find the outcomes so burdensome that they would not participate in the study again
	At least 80% of data is not missing due to attrition or lost to follow-up	At least 50% of data is not missing due to attrition or lost to follow-up	A total of 25% of data is missing due to attrition or lost to follow-up

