#### Patient recruitment, retention, and intervention adherence

This study will determine how long it takes to recruit 24 participants, report how many older adults are screened, and how many meet eligibility criteria. Attendance will be recorded at each exercise session, by the PHCP. If a participant fails to attend an exercise session, the research assistant will contact the participant to record a reason for not attending the session and discuss additional support to attend future sessions to prevent dropout. Study retention rates will report the percentage of participants who complete the 8-week exercise program and provide complete data through follow-up. Data on adherence will be collected using a smartphone application. On completion of each exercise session, participants will scan a unique RedCap-generated QR code that will open a brief survey that will document the completion of the exercise session, completion of each component of the exercise session, and provide feedback on their exercise session adherence.

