### Clinical measures

Clinical outcome measures and exercise program-specific outcomes will be collected at baseline (*diagnostic phase*), 4 weeks, and 8 weeks (post treatment) (Table 4). Outcome measures will include a physical and functional assessment performed by the PHCP and a self-reported questionnaire completed by the participants as suggested by the core outcome sets for low back pain [36] and multimorbidity [37].

**Table 4 Tab4:** Schedule of quantitative data to be collected at baseline and follow-up intervals

	Baseline	4 weeks	8 weeks
Patient demographics	x		x
Physical and functional assessments	x	x	x
Low back pain severity	x	x	x
Oswestry Disability Index	x	x	x
EQ-5D-5L	x	x	x
Clinical frailty scale	x	x	x
Bayliss measure of illness burden	x	x	x
Hospital Anxiety and Depression score	x	x	x
Sit-to-stand test	x	x	x
6-min walk test	x	x	x
Global perceived effect		x	x
Participant satisfaction with treatment		x	x
Adverse events		x	x

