Changes in low back pain will be reported by participants via a daily SMS asking for a numerical ratings scale score (0–10) on the severity of their low back pain throughout the 8-week exercise program. If SMS data identifies an increase in low back pain, participants will be contacted to be asked whether they felt the exercise program may have caused an increase in low back pain. Additionally, the daily SMS will ask about any undesirable experiences related to the exercise program. If the SMS identifies an exacerbation of a comorbidity, the participant will be contacted to be asked about the nature of the adverse event.

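### The 4- and 8-week questionnaires have no stated remote route for participants who miss the visit, which adds avoidable missing data to the Table 2 outcome rows

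*Protocol article*

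**What the plan says.** **Mode.** The Data collection section states: "Data will be collected in person by the research assistant at baseline, 4 weeks, and at 8 weeks", counted from the first exercise session. Under Clinical measures, the outcomes comprise a physical and functional assessment by the PHCP and "a self-reported questionnaire completed by the participants as suggested by the core outcome sets for low back pain". Table 4 schedules the ODI, EQ-5D-5L, Bayliss measure and HADS at baseline, 4 and 8 weeks, and global perceived effect and satisfaction at 4 and 8 weeks. No remote route is described for any of these.

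**What is already collected remotely.** The Adverse events section describes a daily SMS over the 8 weeks that asks for a 0–10 low back pain score. It adds: "Additionally, the daily SMS will ask about any undesirable experiences related to the exercise program". Session adherence is recorded by a phone survey opened with a QR code at the end of each session.

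**Missed sessions.** The section on recruitment, retention and adherence says: "If a participant fails to attend an exercise session, the research assistant will contact the participant to record a reason for not attending the session". The contact also covers support to attend later sessions. Collecting outcomes at that contact is not mentioned. Retention is the percentage of "participants who complete the 8-week exercise program and provide complete data through follow-up".

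**Use of the data.** The Analysis section bases change scores on baseline and 8 weeks. Under Feasibility measures, the Table 2 progression criteria are the primary outcomes. The missing-data row of Table 2 is green when at least 80% of data are present, amber when at least 50% are present, and red at "A total of 25% of data is missing due to attrition or lost to follow-up". The two improvement rows are green at 50% of participants and amber at 25%.

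**The concern.** Self-completed questionnaires do not need a visit, but the plan ties them to one. A participant who does not come at 8 weeks gives no 8-week ODI, EQ-5D-5L or Bayliss score. Even a complete 4-week visit then yields no change score. The daily SMS cannot fill the gap, because it has no item on disability, quality of life or illness burden. The QR survey follows a completed session, so it gives nothing for someone who has stopped attending.

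The affected rows are part of the primary outcome, and one stated aim is to assess the collection and completion of outcome data. If some loss arises only because no link was sent or call made, the missing-data row partly measures the collection mode rather than whether older adults with comorbidity can and will supply the data. With 24 participants, one or two questionnaires can change a colour.

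**Working it through.** **Inputs.** N = 24 (Participants section); Table 2 limits as above; change score from baseline and 8 weeks (Analysis section). The number lost, recovered and improved are assumptions, since the article forecasts none of them.

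**The plan's own figure.** With limits of 45% and 75%, one-sided alpha 0.05 and beta 0.10, the normal approximation gives n = [(1.645 × √(0.45 × 0.55) + 1.282 × √(0.75 × 0.25)) / 0.30]² = 20.95. A continuity correction raises this to 22.6 or 24.2, depending on its form. The stated 24 is therefore reproduced closely enough, and it serves here only as the denominator.

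**Missing-data row, 8-week data.** Share present = (24 − lost) / 24.

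| Lost at 8 weeks | Present | Missing | Table 2 wording met |
|---|---|---|---|
| 4 | 20/24 = 83.3% | 16.7% | green |
| 5 | 19/24 = 79.2% | 20.8% | amber |
| 6 | 18/24 = 75.0% | 25.0% | amber and red |
| 6, with 3 recovered remotely | 21/24 = 87.5% | 12.5% | green |

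Recovering 2 of the 6 would already give 20/24 = 83.3%, which is green. These recovered figures apply to the self-report items. The physical tests of a missed visit stay missing.

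**Sensitivity to what is counted.** Table 2 does not say which time points the row covers.
- 4- and 8-week data, 6 lost after week 4: (48 − 6)/48 = 87.5% present, green.
- 4- and 8-week data, 6 lost before week 4: (48 − 12)/48 = 75.0% present, amber and red.
- All three time points, 6 lost before week 4: (72 − 12)/72 = 83.3% present, green.

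The colour change in the table above therefore holds for a count of 8-week data, and for follow-up data if the loss is early. It does not hold for every reading.

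**Improvement rows, 10 improved and 6 lost.**
- Denominator those observed: 10/18 = 55.6%, green.
- Denominator all enrolled, missing counted as not improved: 10/24 = 41.7%, amber.
- The true share of all 24 lies between 10/24 = 41.7% and 16/24 = 66.7%. Green needs 12/24, that is, at least 2 of the 6 improved. The observed-only reading is thus too favourable if 0 or 1 of the 6 improved, and the all-enrolled reading is too harsh if 2 or more did.

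The width of that interval is (number missing)/24: 6/24 = 25 percentage points without recovery, 3/24 = 12.5 points with 3 recovered. Recovery narrows it whichever denominator is used.

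**The case against.** A reader might infer something stronger: that every outcome is collected only in person, that whoever stops exercising loses all outcome data, and that the improvement rows are therefore biased upward. The article does not support this.

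- The word only does not appear. Pain and undesirable experiences come by daily SMS, and baseline data and any completed 4-week data remain.
- Nothing says that leaving the sessions ends the assessments. The research assistant collects data at fixed time points, PHCPs run the sessions, and withdrawal from the study is a separate, documented step. A person who stops exercising could still attend at 8 weeks.
- Upward bias needs both an observed-only denominator and worse results among non-attenders. Table 2 gives percentages of participants without saying enrolled or observed. If all enrolled are counted and missing means not improved, the rows can only be too low.
- The missing-data row is meant to reflect attrition, so its response to dropout is no error in itself.

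Three further objections carry some weight. In-person collection is a legitimate default: the physical tests require a visit, and one mode is tidy. A remote route would not change retention for those who stop exercising, because the definition also requires completing the program. A journal article may also leave the handling of missed visits to a fuller document. Against this last point, the article states the mode positively rather than leaving it open, and its data-sharing section says that the full protocol will be made available through peer-reviewed publication, which is consistent with this article being that protocol.

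These objections remove the stronger claims. They leave standing that no route is stated for questionnaires that need no visit, in a study that already reaches participants by phone.

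**Conclusion.** The point holds as a cheap improvement, not as an error that invalidates the plan. The 4- and 8-week questionnaires are specified as in person with no remote route. A missed 8-week visit costs the change scores, and part of that loss is avoidable. The size depends on assumptions: with 6 of 24 missing at 8 weeks and half recovered, missing self-report data fall from 25% to 12.5%, which moves the row to green when it is counted on 8-week data. On other readings of the row the colour may not change. No direction of bias in the improvement rows can be asserted; what can be said is that the uncertainty from missing values halves, from 25 to 12.5 percentage points, in the same scenario.

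**What to change.** Keep in-person collection as the default and for the physical tests. Add to the Data collection section: 'Participants who miss the 4- or 8-week visit, including those who have stopped exercising but have not withdrawn consent, will be sent the self-report questionnaires by REDCap link or will complete them by telephone. The mode of completion will be recorded.'

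The cost is protocol and ethics wording and a survey link in a system already in use. The downside is a small mode difference for the few who respond remotely; recording the mode keeps it visible.

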### Feasibility measures

Predetermined progression criteria are the primary outcomes for this study. A traffic light system of green (go), amber (amend), and red (stop) will be used to determine progression of this feasibility study to a fully powered randomised controlled trial (Table 2) [35]. The study will not be feasible to progress if there are intractable issues that cannot be remedied [35].

#### Patient recruitment, retention, and intervention adherence

This study will determine how long it takes to recruit 24 participants, report how many older adults are screened, and how many meet eligibility criteria. Attendance will be recorded at each exercise session, by the PHCP. If a participant fails to attend an exercise session, the research assistant will contact the participant to record a reason for not attending the session and discuss additional support to attend future sessions to prevent dropout. Study retention rates will report the percentage of participants who complete the 8-week exercise program and provide complete data through follow-up. Data on adherence will be collected using a smartphone application. On completion of each exercise session, participants will scan a unique RedCap-generated QR code that will open a brief survey that will document the completion of the exercise session, completion of each component of the exercise session, and provide feedback on their exercise session adherence.

#### Barriers and facilitators for clinicians

One-on-one, semi-structured interviews will be held with PHCPs at the end of the exercise program to discuss the barriers and facilitators of delivering the exercise program.

### Clinical measures

Clinical outcome measures and exercise program-specific outcomes will be collected at baseline (*diagnostic phase*), 4 weeks, and 8 weeks (post treatment) (Table 4). Outcome measures will include a physical and functional assessment performed by the PHCP and a self-reported questionnaire completed by the participants as suggested by the core outcome sets for low back pain [36] and multimorbidity [37].

**Table 4 Tab4:** Schedule of quantitative data to be collected at baseline and follow-up intervals

	Baseline	4 weeks	8 weeks
Patient demographics	x		x
Physical and functional assessments	x	x	x
Low back pain severity	x	x	x
Oswestry Disability Index	x	x	x
EQ-5D-5L	x	x	x
Clinical frailty scale	x	x	x
Bayliss measure of illness burden	x	x	x
Hospital Anxiety and Depression score	x	x	x
Sit-to-stand test	x	x	x
6-min walk test	x	x	x
Global perceived effect		x	x
Participant satisfaction with treatment		x	x
Adverse events		x	x

#### Physical and functional assessment

The participant will perform the standing forward bending test, back extensor endurance test, and the trunk flexor endurance test. The sit-to-stand test will be performed to assess the functional capacity of participants [38]. Participants will be asked to sit in a chair and stand five times without the use of their arms as quickly as possible. This test will then be repeated, and an average test time will be calculated [39]. The 6-min walk test will be carried out by patients on a 30-m walkway to assess aerobic capacity and endurance. The distance covered over a time of 6 min is used as the outcome by which to compare changes in performance capacity. Patients will be instructed to walk their maximum distance in a 6-min period of time. The total distance covered in metres during 6 min of walking will be scored [6].

#### Self-reported outcome measures

Low back pain severity will be assessed using an 11-point numerical rating scale (NRS) ranging from 0 (no pain) to 10 (worst pain imaginable). Two severity questions will be asked at baseline, including current pain and average pain over the last week. Low back pain-related disability will be assessed using the Oswestry Disability Index (ODI). The ODI consists of 10 items representing different health constructs. The total score of the ODI is calculated by adding all scores of applicable items, dividing the obtained score by the maximal total score, and by multiplying the result by 100 to obtain a percentage score [40].

##### Health-related quality of life

The health-related quality of life will be measured using the EQ-5D-5L instrument. EQ-5D-5L is a generic instrument comprised of five questions about mobility, self-care, usual activities, pain and discomfort, and anxiety and depression, each measured on a 5-point scale from no problems to extreme problems. Australian EQ-5D-5L instrument scores are consistent with EQ-5D-5L utility and visual analog scores reported for other countries [41].

##### 
Illness burden

The Bayliss measure of illness burden is used to indicate how much illness affects the participant’s daily life and is measured using a 5-point scale for each individual condition and summed to a total score across conditions [42].

##### Mental health

The Hospital Anxiety and Depression score (HADS) will be used to measure anxiety and depression and has been validated across the lifespan [43]. It consists of 14 items, with scores that range between 0 and 21: scores from 0 to 7 are ‘normal’, from 8 to 10 ‘mild’, from 11 to 15 considered ‘moderate’, and from 16 to 21 ‘severe’ [44, 45].

##### Frailty

The Clinical Frailty Scale will be used to summarise the overall level of fitness or frailty of an older adult [46]. The scale is a way to summarise information from a clinical encounter with an older person, which is useful to screen for and quantify an individual’s overall health status [46].

### Exercise program-specific outcomes

At 4 weeks and 8 weeks, global perceived effect and patient satisfaction data will be collected. Patients will be asked to rate perceived effectiveness on a scale of 1–9, with a score of 1 meaning much better, 5 meaning no change, and 9 meaning much worse [47]. Participant satisfaction with treatment will be measured using the numerical rating scale (0–10), with higher scores indicating greater satisfaction [48].

